#### Secondary outcomes

Speed of appropriate EMS dispatch: speed will be measured using time-stamped data from start of 999 calls to appropriate deployment with judgement of ‘appropriateness’ to be based on algorithms developed through expert consensus (see below) and using medical records data up to 3 months post-incident where consent is provided; stand-down rate (de-escalation); missed jobs (eg, not prioritised for HEMS/CCP despatch, either due to lack of resource or inappropriate prioritisation); requests for further ambulance resources from scene. Psychological harm will be assessed using two validated scales^24 25^ pre-trial and post-trial in 999 callers from both arms and staff viewing the footage (including staff in comparison EOC).

The appropriateness of dispatch will be determined based on algorithms developed through expert consensus before the trial starts. Appropriateness is defined as the need for intervention and/or transport by the response vehicle/staff dispatched to scene (eg, for HEMS dispatch that a critical care intervention and/or transportation by helicopter was required^9^). A binary outcome decision tree will be developed with the reasons for appropriate/inappropriate dispatch categorised and agreed (inappropriate dispatch will be further categorised as being ‘over’ or ‘under’ resourced).

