## Introduction

### Background and rationale

Emergency medical services (EMS) provide emergency medical care at the scene of incidents before patients are conveyed to hospital (eg, blood transfusions and emergency anaesthesia). To save lives and prevent long-term disability, timely and accurate dispatch of pre-hospital resources is critical.^1^ Evidence suggests trauma patients should receive definitive care within 1 hour of the incident (The ‘Golden Hour’), otherwise the risk of morbidity and mortality increases significantly.^2^ Where severe injury is suspected by EMS (eg, major trauma), specialist paramedics in critical care and/or helicopter EMS (HEMS) may be dispatched to the scene to care for the patient and/or convey the patient to hospital.

When a 999 call is made in the UK, the dispatchers in the emergency operations centre (EOC) need to decide which resources to send to the scene by gathering information about what has happened and the clinical state of the patient(s). The dispatchers rely on 999 callers and other bystanders to accurately relay essential information.^3^ However, lay public 999 callers can sometimes provide inaccurate information due to language barriers, subjectivity, the emotional impact of being at the scene and limited medical training or knowledge.^3 4^ Dispatch response is often recognised as a weak link in the EMS chain,^5^ often involving either under-resourcing or over-resourcing.^6–9^ Previous studies have shown that up to 50% of HEMS (air ambulance) dispatch and 25% of road ambulance dispatch for suspected trauma patients are not appropriate.^6–9^

It is vital that EMS are being dispatched to incidents where they are needed due to finite and often limited resources. If dispatchers were able to see the patient and scene via live video streaming through a 999 callers’ smartphone camera, it could be easier to make more accurate and timely decisions about dispatch of EMS.^4^ There is evidence that video-assisted cardiopulmonary resuscitation (CPR) has the potential to improve patient outcomes,^10–16^ but there is a lack of research evidence to support the use of live video streaming for EMS dispatch for trauma.

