### Intervention and randomisation

999 calls in the main trial site during the six observation weeks (up to 42 days; 84 shifts) will be randomised 1:1 to working shift intervention or standard care. Control shifts will follow standard care ambulance dispatch protocol with a 999 caller using a telephone (voice only) and the call taker using NHS Pathways ambulance dispatch tool.

In the intervention arm, a live streaming technology called GoodSAM Instant-on-Scene^23^ will be tested. The technology allows a 999 caller to stream live video footage from the scene of an incident to the EOC. 999 calls allocated to intervention will initially follow the standard NHS Pathways dispatch protocol until ambulance dispatch prioritisation has been determined. EMS will be dispatched as normal, without delay. The call handler in the EOC will then transfer the caller to the HEMS dispatcher or critical care paramedic (CCP) and live streaming will be activated. EMS resource allocation may be adjusted following this.

If at any point the dispatcher feels they do not want to view the scene (eg, due to psychological impact of viewing the scene) or it is not safe to continue, the 999 caller will be thanked for their help and the call will be ended. The dispatchers will be provided with training and guides outlining the trial processes to ensure adherence to intervention and study protocols.

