### Statistical methods and data analysis

#### Quantitative analysis

A full statistical analysis plan (SAP) will be reviewed by key members of the research team and approved by the steering committee before analysis is undertaken.

As this is a feasibility study, statistical analysis will focus on providing estimates and confidence intervals of key rates such as the number of eligible calls per day, uptake of video intervention and timing and appropriateness of dispatch to inform a subsequent RCT. Outcome measure will be summarised by arm and estimates reported with confidence intervals to inform future sample size calculations.

The SAP will outline any expected exploratory analysis of outcomes that may be useful to inform a subsequent RCT including any signal of potential efficacy, but it is noted that the study is not powered for this and so any interpretation would be limited to the direction and magnitude of any effect. Missing data (including outcome data) will be summarised, but all observed data will be included in any analysis according to the randomised allocation following the intention-to-treat principle.

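### Speed is timed to an appropriate deployment, so incidents that never receive one have no value and the comparison of arms rests on groups formed after randomisation

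*Protocol article*

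**What the plan says.** The protocol article, under Secondary outcomes, fixes both ends of the speed measure: "speed will be measured using time-stamped data from start of 999 calls to appropriate deployment". The end point depends on a judgement made afterwards with expert-consensus algorithms and, where consent is given, medical records: "Appropriateness is defined as the need for intervention and/or transport by the response vehicle/staff dispatched to scene". The rating is binary and failures are expected: "inappropriate dispatch will be further categorised as being" over- or under-resourced. The same section lists a separate outcome for "missed jobs (eg, not prioritised for HEMS/CCP despatch, either due to lack of resource or inappropriate prioritisation").

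Under Intervention and randomisation, calls in the intervention arm first go through the standard dispatch process. Live streaming is activated after that, and "EMS resource allocation may be adjusted following this".

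Under Quantitative analysis, "Missing data (including outcome data) will be summarised, but all observed data will be included in any analysis according to the randomised allocation", in line with intention to treat. Timing and appropriateness of dispatch are among the quantities to be estimated for a later trial. For any efficacy signal, "any interpretation would be limited to the direction and magnitude of any effect". Objectives and research questions lists effect size and precision among the data needed to design that trial.

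**The concern.** An incident that is missed, or is under-resourced and never corrected, does not reach the end point. The article gives it no value, censoring rule or composite. Under an observed-data rule it would simply not contribute to speed. Yet it is not missing in the usual sense: it is a known failure, the worst result possible on this outcome.

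Whether an incident has a time depends on appropriateness, which is settled after randomisation and which streaming is intended to improve. Labelling incidents by randomised arm does not restore comparability if each arm contributes only its successes. The design also suggests a direction. Streaming follows standard dispatch, so an incident corrected because of the footage enters with a later time than one that was right first time, while a control incident of the same kind that is never corrected enters with no time at all. At stake are the direction and magnitude of the speed effect, the two features the article says it will interpret.

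**Working it through.** **1. The plan's own precision figures (Sample size).** Inputs: 250 incidents, 125 of them in the intervention arm, over 42 days.

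- Event rate, Poisson, 95% level assumed: 1.96 × √250 / 42 = 0.738 per day, which agrees with the stated ±0.75.
- SE below 5% for speed: the article gives no scale or standard deviation. Read as a worst-case proportion (an assumption), √(0.25/125) = 4.47%, which agrees.
- On that reading the SE stays below 5% only with more than 0.25/0.05² = 100 incidents per arm. That allows fewer than 25 of 125 (20%) to be without a value, before any allowance for shift clustering.

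**2. Mean time among appropriately deployed incidents.** All inputs here are assumed; the article gives no times or rescue rates. Let a share p of control incidents be appropriately deployed with mean t₀ = 10 min. In the intervention arm the same share is g min faster, and a further share r is rescued with mean t₀ + L. Control has no late corrections in this version.

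Intervention mean = [p(t₀ − g) + r(t₀ + L)] / (p + r)

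Difference, intervention minus control = (rL − pg) / (p + r)

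Speed-up at which the difference is zero: g = rL/p

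| p | r | L (min) | Difference, g = 0 | Difference, g = 1 | Break-even g |
|---|---|---|---|---|---|
| 75% | 5% | 5 | +0.3 | −0.6 | 0.3 |
| 75% | 10% | 10 | +1.2 | +0.3 | 1.3 |
| 75% | 20% | 10 | +2.1 | +1.3 | 2.7 |
| 50% | 5% | 5 | +0.5 | −0.5 | 0.5 |
| 50% | 10% | 10 | +1.7 | +0.8 | 2.0 |
| 50% | 20% | 10 | +2.9 | +2.1 | 4.0 |

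A positive difference means that the intervention looks slower, although no incident is worse off in any row. With a 1 min gain elsewhere the sign reverses in four of the six rows. In the other two it is right, but the gain is understated.

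**3. Late corrections in control.** If a share c of control incidents is also corrected L min late, the difference at g = 0 becomes L[r/(p + r) − c/(p + c)]. With p = 75%, r = 10%, L = 10 and c = 5% (assumed), this is 10 × (0.10/0.85 − 0.05/0.80) = 10 × (0.1176 − 0.0625) = +0.55 min, against +1.18 min with c = 0. With c = r it is zero. Late corrections in control therefore shrink the bias and can remove it.

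**4. Keeping every incident.** Simulation of 2,000,000 incidents per arm: gamma times with mean 10 min, p = 75%, a gain of up to 1 min, and 10% rescued 10 min later.

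| Summary | Control | Intervention |
|---|---|---|
| Mean among appropriate only | 10.0 min | 10.5 min |
| Median among appropriate only | 9.2 min | 9.0 min |
| Median, all incidents | 11.4 min | 10.4 min |
| Appropriately deployed by 20 min | 71.8% | 78.3% |
| Mean restricted to 60 min, all incidents | 22.5 min | 17.9 min |

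The conditional mean has the wrong sign. The conditional median has the right sign but shows 0.2 min where the all-incident median shows 1.0 min. Every summary that keeps all incidents favours the arm that is in fact better.

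**The case against.** The strongest reply is that the article never says these incidents are excluded. It gives a start and an end, and a time to an event is compatible with censoring or with counting an incident as not reached. A full SAP is promised and could do either. No mean or median by arm is specified, and the SE below 5% can be read as a proportion over all incidents, which is close to the remedy below. This stands as a limit: the exclusion is implied, not stated. It does not remove the point, because the end point itself is fixed in this text, and the only rule stated for outcomes without a value is the observed-data rule.

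Four stronger readings are tempting and are not supported.

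- A reader might infer that every inappropriate dispatch lacks a time. An over-resourced incident may still have had a needed vehicle deployed at a recorded time; the article does not say which time stamp would count.
- A reader might take the loss to be 25% to 50% of incidents, from the background statement that "up to 50% of HEMS (air ambulance) dispatch and 25% of road ambulance dispatch for suspected trauma patients are not appropriate". Those are upper limits on shares of dispatches in earlier studies, not shares of incidents that never received an appropriate resource.
- A reader might infer that streaming will look slower. Requests from scene for further resources are themselves an outcome, so control incidents can also be corrected late, and a real speed-up elsewhere can outweigh the effect.
- A reader might take speed to be the definitive trial's main outcome. The article does not say so.

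It is also fair that missed jobs and appropriateness are reported alongside speed, so a reader would see them. That helps interpretation but does not repair the speed estimate.

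**Conclusion.** The point holds in this form: as defined, speed has no value for incidents that never receive an appropriate deployment, and under the stated observed-data rule a time summary by arm conditions on a post-randomisation result that the intervention is meant to change. The resulting bias may reverse the sign or only understate the gain. In the scenarios shown, with a 1 min gain elsewhere, the difference in means runs from −0.6 to +2.1 min on a control mean of 10 min. These figures rest on assumed times, rescue shares and delays and on no late corrections in control; the trial's actual bias cannot be derived from the article.

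The consequence is moderate. Speed is a secondary outcome of a feasibility trial and is not in the Table 3 progression criteria. It still merits correction before analysis, because its direction, magnitude and precision are meant to feed the design of the definitive trial.

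**What to change.** Define the speed outcome for every randomised incident. Report by arm the cumulative proportion with the appropriate resource deployed by fixed times from the start of the call, or the restricted mean time to a fixed horizon, and count never-appropriate incidents as not reached throughout. Give the difference between arms with a confidence interval that allows for clustering by shift, since shifts are the main unit of randomisation. State which time stamp applies to over-resourced incidents. Report time among appropriate deployments only as a description, next to the number of incidents it covers.

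The time stamps and appropriateness ratings are those already planned, so the change is one of outcome definition and SAP wording. The cost is a slightly less familiar summary.

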### Participant timeline

There will be six trial weeks, 1 week a month from June to November 2022. Each trial week will include up to 14 randomised shifts (day and night). EOC staff in the main trial site and staff well-being substudy will be invited to participate in the staff survey pre-trial and post-trial period. Staff in the main trial site will be invited to partake in interviews through the survey. 999 callers in the main trial site will be sent a text message after the eligible incident inviting them to participate in a survey 6–8 weeks post incident and a subsequent interview. Patients will be approached for consent for their medical records to be accessed up to 3 months after the incident has occurred.

In the observational substudy, EOC staff will be observed using GoodSAM live streaming over a 3-month period and invited to partake in interviews. 999 callers will be invited to partake in the survey within 1 week of the incident they called 999 for and subsequently invited to partake in an interview about their experiences of using GoodSAM live streaming.

### Sample size

We estimate there will be approximately 250 trauma incidents (including 300 patients) over the six observation weeks (125 allocated to intervention), which will allow for an estimate of true event rate within precision of ±0.75 events per day; and allow estimation of speed to appropriate response with an SE of <5%. These sample size estimations are based on convenience sampling over the six defined trial observation weeks. We estimate there will be approximately 350 lay public 999 callers (250 from the main trial site and 100 from the observational substudy) and up to 202 EOC staff (86 from the main trial site, 30 from the observational substudy and 86 from the third EOC).

### Recruitment: identification and consent

#### Trauma patients

Trauma patients will be identified by research paramedics (RPs), using the eligibility criteria. RPs will observe all trial shifts. For eligible calls in the main trial site, the computer-aided dispatch (CAD) number(s) relating to the incident will be recorded by the RP as the identifier to share with the conveying hospital to approach for consent. Informed consent will be sought from either the patient, their consultee or the patient’s parent or guardian (either in the hospital before discharge or via telephone, email or post) in all hospital trusts included in the trial (trauma units and major trauma centres covered by the EOC). RPs may consent patients in person with assistance from the hospital to identify the patient(s). Approval has been granted by the Confidentiality Advisory Group (Section 251 application) to access medical records for casualties who die before consent can be sought (and where there is not a power of attorney in place for that individual). National data opt-out status will be checked for all deceased patients.

#### 999 callers

In the main feasibility site, the RP will determine eligibility of the 999 callers and prompt the dispatchers to send a text message via the CAD, inviting the 999 caller to participate in a survey about their experience of calling 999 for the incident. The text message will include a link to the participant information sheet (PIS), consent form and contact details for the research team. A reminder text message will be sent to 999 callers within 1 week of the incident. Those who participate in the survey will be invited to partake in an interview and selected to represent a range in demographics (age, ethnicity, gender), type of incident they witnessed and evidence or not of psychological harm from survey responses.

In the inner-city observational substudy, at the end of the call (once resources have been dispatched) 999 callers will be asked for permission to store their name and number to share with the researcher to be invited to participate in the study. Those who consent will initially be contacted by phone so the researcher can explain the study and ask their permission to send them further details about the study via text message or email. The researcher will then send a text message or email with a link to the PIS and consent form, which once completed will re-direct to the survey. Reminder texts/emails will be sent up to 1 week after the incident. Only those who participate in the survey will be invited to partake in an interview.

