#### 999 callers

999 callers in the main trial site will be invited to complete surveys via Qualtrics online survey software^32^ 6–8 weeks post incident to assess psychological harm and semistructured interviews regarding experiences and acceptability of the use of live streaming. The questionnaire will include demographic questions, The Impact of Events Scale—Revised,^24^ The General Health Questionnaire-12 item version^25^ and questions about acceptability and experience of live streaming.

In the inner-city observational substudy, 999 callers will be invited to complete surveys via Qualtrics^32^ up to 1 week after the incident. The questionnaire will include a demographic questionnaire and questions about their experiences of using live streaming during their recent 999 call for example, ease of use, usefulness. Those who take part in the questionnaire will be invited to participate in an interview regarding experiences and acceptability of using live streaming.

999 callers at both sites who participate in the survey will be offered the choice of a £10 shopping voucher or £10 donation to the local air ambulance charity. A second voucher or donation will be offered to those who complete an interview.

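### The main-site caller harm survey is set at 6–8 weeks, but the only stated reminder falls within 1 week, and the article's statements on the timing of caller harm do not agree

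*Protocol article*

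**What the plan says.** Four parts of the protocol article bear on when caller harm is measured at the main site, and two more on how the result is used.

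- **Participant timeline.** Callers will be "sent a text message after the eligible incident inviting them to participate in a survey 6–8 weeks post incident".
- **Data collection methods, 999 callers.** Callers are to be invited to online surveys "6–8 weeks post incident to assess psychological harm". The questionnaire contains the Impact of Events Scale—Revised and the GHQ-12.
- **Recruitment, 999 callers.** The research paramedic will "prompt the dispatchers to send a text message via the CAD". On content: "The text message will include a link to the participant information sheet (PIS), consent form and contact details for the research team". On follow-up: "A reminder text message will be sent to 999 callers within 1 week of the incident".
- **Secondary outcomes.** The two scales are said to be applied before and after the trial, in callers from both arms as well as in staff.
- **Table 3, row 4.** Harm in callers who use live streaming must not be significantly greater than in those who do not. The row has a green and a red level but no amber one.
- **Quantitative analysis.** All observed data enter the analysis by randomised allocation. No limit on the timing of a response is mentioned.

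**The concern.** A reminder sent by day 7 suits a survey that is answered in the first week. That is the schedule of the inner-city substudy, whose survey and reminders both run up to 1 week and for which the article lists no harm scales. It does not suit a survey due on days 42–56.

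The article does describe a later contact elsewhere: staff who leave an email address are sent the post-trial link. The substudy also asks callers for permission to keep their name and number. The recruitment section gives no comparable later step for main-site callers.

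Distress in the first days after witnessing major trauma and distress at 6–8 weeks are different outcomes. If row 4 pools them, a difference between groups in how soon callers answer could pass for harm or benefit from streaming. If few callers answer in the window, a finding of no significantly greater harm says little, yet it would count as green.

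**Working it through.** **1. Dates.** The survey window is 6 × 7 = day 42 to 8 × 7 = day 56. The reminder falls on day 7 at the latest. The gap is therefore at least 42 − 7 = 35 days to the opening of the window and at least 56 − 7 = 49 days to its close. The invitation has no exact time, but it precedes its reminder, so it also falls in the first week.

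**2. Do the statements fit together?** Participant timeline and Data collection agree on 6–8 weeks. The recruitment section places its invitation and reminder in week 1. Secondary outcomes gives a before-and-after schedule that cannot apply to callers, who are identified only through the incident. The 6–8 week statements and the week-1 texts can be reconciled if the texts concern consent only. The before-and-after statement cannot be reconciled with a single post-incident survey.

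**3. If the survey can be answered on first contact.** Let e1 and e0 be the shares answering early among callers with and without streaming. Let pE and pL be the harm rates in week 1 and at 6–8 weeks, equal in both groups (no true effect). Then

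observed difference = (e1 − e0) × (pE − pL).

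The article gives none of these rates. With assumed pE = 40% and pL = 15%:
- Equal early shares give a difference of 0. The level is still wrong: at 30% early it is 0.3 × 40 + 0.7 × 15 = 22.5%, not 15%.
- Early shares 10 points apart give 0.10 × 25 = 2.5 points.
- Early shares of 60% and 30% give 0.6 × 40 + 0.4 × 15 = 30.0% against 22.5%, a difference of 7.5 points.

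**4. If the survey opens only in the window.** The Sample size section expects 250 main-site callers and about 250 incidents, 125 of them allocated to intervention. Its precision figure reproduces: 250/42 = 5.95 per day, half-width 1.96 × √250/42 = 0.74, against ±0.75 stated. Taking 125 callers per group and an assumed response rate r, n = 125r. The detectable increase p1 − p0 (two-sided 5%, 80% power) solves

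p1 − p0 = 1.96 × √[2p̄(1 − p̄)/n] + 0.84 × √{[p0(1 − p0) + p1(1 − p1)]/n}, with p̄ = (p0 + p1)/2.

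With an assumed p0 = 20%:

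| Response r | n per group | Detectable increase (points) |
|---|---|---|
| 100% | 125 | 15.9 |
| 50% | 62.5 | 23.1 |
| 30% | 37.5 | 30.5 |
| 20% | 25 | 37.8 |
| 10% | 12.5 | 53.4 |

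Clustering by shift is ignored, and the approximation is rough in the last row. Steps 3 and 4 show that timing and response would matter. They do not show that early completion or low response will occur.

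**The case against.** The strongest reply is that the article describes a two-step process. The main-site text is said to link to the information sheet, consent form and contact details, with no survey link named. Only for the substudy does the article say that the consent form leads straight on to the survey. The Data collection section says callers will be invited to surveys at 6–8 weeks, which can be read as a separate invitation at that time. The 1-week reminder would then chase consent, and an early reminder would be sensible. How the link is delivered is detail that an article may leave to the full protocol, which it cites.

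Much of this stands. A reader might infer that all contact ends by day 7, and that the harm criterion therefore rests on early or missing responses. The document does not support that: it does not say that the survey opens at the invitation, it allows a later invitation, and it gives no response rate. Nor does it follow that the trial cannot address caller harm, since interviews and free text also inform the progression decision.

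The reply does not remove the mismatch. The article chose to state a reminder time, and that time does not serve the stated survey time. The consent-only reading has to be assembled from three sections and is stated in none. It leaves the before-and-after schedule for callers unexplained, and the rule that all observed data are included would admit an early response.

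**Conclusion.** The point holds as a moderate one. As written, the only stated reminder precedes the survey window by at least 35 days, and the sections on caller harm timing do not agree. They feed a go/stop criterion with no amber level, under an analysis rule that sets no timing limit.

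The consequence is conditional. If callers can complete on first contact, row 4 mixes acute with 6–8 week distress. If they cannot, the stated reminder does nothing for response in the window. Neither effect can be sized from the document. The 0 to 7.5 point range rests on assumed harm rates and early shares, and the 15.9 to 53.4 point range on an assumed 20% control rate and assumed response of 100% down to 10%.

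**What to change.** - Reconcile Secondary outcomes, Participant timeline, Recruitment and Data collection so that one timing is given for caller harm, and remove the before-and-after wording for callers.
- State that the post-incident text and the 1-week reminder are for information and consent.
- Send the survey link at 6 weeks, with a reminder inside the 6–8 week window.
- Record the completion date of every survey.
- Base row 4 of Table 3 on responses completed in the window, and report any earlier ones separately.

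The cost is one rescheduled or added text and one date field. The small downsides are that contact numbers are held until week 8 and that out-of-window responses do not count towards row 4. For callers whose texts have already gone out, the last two steps can still be written into the SAP, which the article says is approved before analysis, provided completion dates are available.
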